**Discussion:**

The primary output will be development of an integrated programme of interventions to improve pregnancy preparation, pre-pregnancy care uptake, and reduce adverse pregnancy outcomes in women with T2DM. We will also develop an implementation plan to support the introduction of the interventions across the NHS.

**Trial registration:**

ISRCTN47576591; February 8, 2022.

## Background

As the prevalence of Type 2 diabetes (T2DM) continues to increase [1], the age of onset has also been reducing [2]. Consequently there are now many more women of reproductive age living with T2DM, with half of pregnancies in women with pre-existing diabetes in England and Wales now occurring in women with T2DM [3]. This proportion is greater in areas such as London where 70% of pregnancies are in women with T2DM [3], due to the higher numbers of women of Black or Asian ethnicity as these populations tend to have an earlier age of onset [2, 4]. Diabetes pregnancies are associated with multiple hazards and higher care costs. Compared to women without diabetes, women with diabetes have: double the risks for congenital abnormality or stillbirth [5–10] and a quadrupled risk of fetal death [5, 6]. Concerningly, these adverse outcomes are increasing, with no progress having been made in the last two decades [11]. These risks are now more evident in women with T2DM, as the proportion of stillbirths and neonatal deaths is higher in women with T2DM compared to those with Type 1 diabetes (T1DM) [3, 5]. The most recent National Pregnancy In Diabetes (NPID) audit of pregnancy outcomes in women with T2DM reported that: 26% of pregnancies resulted in large for gestational age (LGA) babies; 50% of births were by caesarean section; and 15% of infants are admitted to neonatal care [3, 12]. Hence, diabetes pregnancies in women with T2DM are increasing, these are high risk, currently have poor pregnancy outcomes and are associated with increased treatment costs.

Many of the risks associated with diabetes pregnancies can be ameliorated with improved pregnancy preparation and specific pre-pregnancy care clinic attendance. It is well established that exposure to hyperglycaemia and some treatments prescribed in the management of T2DM can harm the fetus during the period of organogenesis in the first trimester [13, 14]. Unfortunately, many women with T2DM are unaware of these risks [15] and may not realise they have conceived until late into the first trimester of their pregnancy [16]. In response, the National Institute for Health and Care Excellence (NICE) has developed guidelines for pre-pregnancy care (PPC) in women with diabetes which recommends: initiating high-dose (5 mg) folic acid; avoiding teratogenic medications; and intensifying glucose control [17]. However, the uptake of PPC is very low in the UK, with only 10% of women with T2DM meeting the current NICE criteria [3] increasing the risk of adverse pregnancy outcomes [18, 19]. It is also concerning that the majority of these women are from deprived areas and are from Black or Asian minority populations, thereby heightening underlying health inequalities [3]. Hence, establishing effective interventions to improve the uptake of PPC in women with T2DM is a high priority.

Previous prospective cohort studies investigating interventions to improve PPC uptake in women with diabetes have had a limited impact among women with T2DM, increasing uptake by only 7–15% [20–23]. These interventions have included: health professional education; patient information and education on PPC; PPC teams; and clinical guidelines [20–23].

In the most recent UK study, while there was a significant improvement in 'optimal' pregnancy preparation among women with T2DM (5.8% and 15.1%; *p* = 0.021), defined as having HbA1c ≤ 48 mmol/mol (6.5%), on folic acid 5 mg daily and not taking harmful medications prior to last menstrual period, and attend antenatal care at ≤ 8 weeks gestation, the majority of this group (85%) were not optimally prepared for pregnancy, with no significant changes in teratogenic medicine exposure (16% before and 12.2% during/after PPC implementation; *p* = 0.41) [23]. Limitations of these studies included: a failure to consider the behavioural factors that mediate PPC uptake in the context of women with T2DM, health professionals or the care system; and that they focussed on both women with T1DM and T2DM where the care contexts are quite divergent. In women with T2DM it is important to integrate PPC into primary care as this is where most women receive diabetes support, in contrast to those with T1DM who are managed in specialist services, in the UK. In addition, it is also important to consider women’s cultural beliefs and context as these can have a powerful influence on their reproductive health behaviours [15]. Therefore, if the uptake of PPC in women with T2DM is to be improved a new approach is required. Hence, we have developed an intervention programme that is exclusive to women with T2DM and has been theoretically modelled to specific target behaviours with a focus on primary care; this programme is called PREPARED (**PRE-P**regnancy c**ARE** for women with type 2 **D**iabetes).

## Development of PREPARED

The PREPARED programme is comprised of an integrated portfolio of interventions developed following the Medical Research Council (MRC) complex interventions framework [24], based on preliminary theory and modelling work that included: a systematic review of previous interventions [25]; a meta-synthesis of women’s experiences of PPC [26]; and a qualitative study with women with T2DM (*n* = 30) and health professionals (*n*= 22) exploring experiences of PPC and how to improve PPC uptake [15, 27]. The data from this work were used to develop a logic model mapping the key factors that mediate PPC uptake in relation to the women, health professionals and the care system. The intervention components were then integrated into the model targeting different mediating factors (see Fig. 1). As many of the mediating factors were behavioural or related to care systems, we also modelled the programme using: the COM-B (capability, opportunity, motivation to perform a behaviour) and the Behaviour Change Wheel (BCW) frameworks [28]; and Normalisation Process Theory [29, 30].

**Fig. 1 Fig1:**
[figure not shown]
Integrating areas of potential intervention

Throughout the development of the intervention, we have also been working with a group of women with T2DM who have experienced a diabetes pregnancy. Together with them and health professionals from primary care, diabetes services and maternity care we have built the PREPARED intervention, which is comprised of the following theoretically modelled components:decision support systems to prompt pregnancy review in primary care;an integrated primary care care-pathway for PPC linking to diabetes intermediate care teams, women’s health and maternity services;reproductive intention and pregnancy reviews with collaborative care-planning for all eligible women;materials for promoting pregnancy awareness in women with T2DM;web-based information resources for women;and performance monitoring with feedback to practices on PPC activity and pregnancy outcomes.

The most important feature of our approach is that it is centred in primary care where the women receive their routine diabetes management, rather than hospitals where most PPC is currently provided. PREPARED involves installing interventions to promote PPC within the electronic management systems of general practices in primary care, along with a training package for the practice team. In this paper we outline the protocol for a study which will aim to optimise the different components of the PREPARED intervention by assessing their impact on women’s access to PPC (or contraception) and pregnancy outcomes. The study will start in October 2021 and is funded by the UK government through the Health Services and Delivery Research programme of the National Institute of Health Research (NIHR131250).

## Methods

### Study approach

Reflecting the multimodal nature of the PREPARED programme and the complex care context for our study, we have designed the study following Complex Adaptive Systems (CAS) theory. CAS is an emerging model for evaluating complex interventions that considers: interdependencies within the studied system; the role of learning; interactions in self-organisation (stable/dynamic) among system components; emergence, the way different intervention components might interact leading to unexpected outcomes; and co-evolution, the way the system adapts to the intervention components and vice versa [31]. CAS theory allows interventions to be developed iteratively by boosting or optimising intervention components based on performance during the evaluation period. For this study we will use a blended approach based on complexity and implementation science, as advocated by Braithwaite et al. (2018); [32] with an integrated process evaluation following the MRC process evaluation model for complex interventions [33]. To address the implementational element within the study we have used Normalisation Process Theory (NPT) [29, 30] to study the performance and adoption of the PREPARED intervention, considering: coherence (differentiation, specification and internalisation); cognitive participation (initiation, enrolment and activation); collective action (workability and integration); and reflexive monitoring (systematisation and appraisal). A preliminary economic evaluation in the form of a cost consequences analysis will summarise costs and outcomes to inform future definitive evaluations of cost-effectiveness of the PREPARED intervention.

### Study objectives

The study aims to optimise the PREPARED intervention components and to estimate their impact on the uptake of PPC and pregnancy outcomes. The study objectives are to:observe the impact of the intervention components and iteratively optimise their effect on care processes and outcomes;assess intervention feasibility (acceptability, utility, reach, and fidelity);understand the organisational factors that mediate intervention implementation and performance;study the impacts of intervention components on the behaviours of health professionals and women with T2DM;generate theoretical models for implementing PPC;and undertake preliminary estimation of intervention costs and benefits.

### Study design

A multimethod design will be used, with a clinical audit of PPC related processes and outcomes; and an integrated process evaluation informing intervention feasibility, implementation, and behaviour change; and an economic cost consequences analysis. The clinical audit will provide PPC performance data. Following CAS theory, we will use frequent repeat measures of the PPC performance metrics to monitor the delivery and impact of the intervention components at four-monthly intervals over 18 months from baseline (performance 12 months pre-intervention). At each timepoint performance measures will be reviewed to inform where intervention effects might need boosting or refining. The target performance for the intervention will be a minimum improvement of 30% at final observation in the proportion of women meeting current NICE pregnancy criteria [17]. Practice level performance will also be monitored considering the number of women: having a reproductive review; accessing PPC; receiving folic acid 5 mg; and instigated on contraception. Table 1 provides an overview of the data that will be used to determine systemic (across the exposed practices) and practice level performance (see Table 1). The PPC and pregnancy outcomes will have a relatively low incidence at the practice level so these will only be considered at the systemic level.

**Table 1 Tab1:** Performance measures

Performance measures	Systemic Performance	Practice Performance
Process data		
• Reproductive review and care plan instigated	Yes	Yes
• Care pathway activation	Yes	Yes
• Initiation of folic acid 5 mg	Yes	Yes
• Contraception advise given	Yes	Yes
• Instigated on contraception	Yes	Yes
• HbA1c testing and results	Yes	Yes
Pre-pregnancy care targets		
• HbA1c ≤ 48 mmol/mol (6.5%)	Yes	No
• Prescription of 5 mg folic acid pre-pregnancy	Yes	No
• Cessation of potentially teratogenic therapies	Yes	No
Pregnancy outcomes		
• Neonatal hypoglycaemia	Yes	No
• Macrosomia (birth weight > 4.5 kg)	Yes	No
• Shoulder dystocia	Yes	No
• Caesarean section incidence	Yes	No
• Neonatal intensive care admissions	Yes	No
• Postnatal length of stay	Yes	No
• Any other adverse outcomes	Yes	No

The process evaluation will assess: the reach, fidelity, delivery and receipt of the programme; the women’s and health professionals’ experiences of the interventions; mechanisms of action, including changes in women’s and health professionals’ behaviours; and system level interactions. Data will also be collected on how the intervention affects the ability of clinicians to anticipate and respond to women’s needs, monitor performance, and learn from positive and negative outcomes, which are key characteristics of adaptive systems [34, 35]. The process evaluation will use a mixed-method approach incorporating both qualitative and quantitative data which will be collected at multiple time points to provide opportunities for data triangulation and subsequent theory generation [33]. An overview of the study design is presented schematically in Fig. 2.

**Fig. 2 Fig2:**
[figure not shown]
Study flowchart

### Study setting, sample size and participants

The study will take place in South London where currently a high proportion of women with T2DM become pregnant without effective PPC [3]. We will recruit 30 general practices for intervention exposure. Practices will be considered for inclusion if they have ≥ 25 women with T2DM of reproductive age (18–45 years), this will provide a pooled sample of 750 women. Two local hospital diabetes pregnancy services responsible for the maternity care of 80–100 women with T2DM per year from this area will also participate, so that pregnancy outcomes can be studied.

It is difficult to predict how many women will be actively trying to conceive during the study period (this will be an important finding in itself), but we have estimated based on the number of annual pregnancies reported there will be 120–150 pregnancies in the participating boroughs: with 40–50 pregnancies in the women attending the PREPARED exposed practices. If we assume that women will be trying for pregnancies for 12 months prior to conception, then we can further estimate that > 100 women will be requiring PPC intervention with the remaining women (*n* =  > 650) requiring reproductive review and contraception.

There are high levels of deprivation and ethnic diversity in the local area, hence, establishing intervention reach into these communities is an important objective for the study as these groups of women form a major proportion of the target population.

### Data collection

The audit data (see Table 1) will be extracted from participating practices using an electronic template that we will install in the participating practices electronic record keeping system, the data collected will identify: women of child bearing age (< 45 years) attending appointments; reproductive assessments (activated on template); glycaemic control; changes to medications or contraception; PPC care-plan initiation; and PPC education or the dispensing of the integrated PREPARED self-help resources (leaflets and web-links). The pregnancy and pregnancy outcome data will be collected from the participating hospital audit systems which routinely collect these data for all women with diabetes as part of an ongoing national audit. The pregnancy booking data includes: glycaemic control; folic acid (5 mg) adherence; the prescription of any teratogenic therapies; and estimated pre-pregnancy weight. The birth outcome data includes: term and status of infant at birth including details of adverse outcomes; mode of birth; breast feeding status; maternal health/injury and depression; pregnancy complications; length of hospital stay; and neonatal care admissions. We will collect these data on all births during the observation period so we can compare outcomes in women from the intervention practices to unexposed practices. The hospital and practice level data will be extracted at baseline (12-month pre-PREPARED exposure) and then monthly to generate run charts monitoring process and outcome performance, with a full audit and review each quarter. The monthly data extractions will be continuous throughout the observation period (18 months). All data will be anonymised at source by hospital/practice administrators, practice codes will allow us to link them to the hospital data.

The unit of observation for determining performance within the audit will be the patient level care events of interest (i.e., a recorded occurrence of care actions or outcomes of relevance to the study performance outcomes). These data will be used to assess performance at two levels: the systemic level; and the practice level. The systemic level analysis will use the aggregated data from the participating practices detailing intervention impact on the activation of care processes and clinical outcomes, at the performance monitoring intervals to the study endpoint. The data will be used to populate run charts which will be updated monthly so that performance can be continuously assessed. The practice level data will enable us to consider inter-practice differences and the factors that may contribute to variations in performance between them. As the intention of this intervention is ultimately to improve local and national performance in achieving pre-pregnancy care targets and reduce adverse pregnancy outcomes, the primary estimate of impact will be at the systemic level. It should be noted that practice level feedback is also one of the intervention components; the practices will be able to see how well they are performing to either reaffirm progress and/or to stimulate further activity in achieving their performance goals.

The process evaluation data will involve qualitative and quantitative data collection using tools, and analytic models that have been designed following CAS [31], NPT [29, 30] and COM-B frameworks [28]. The qualitative data will include:Interviews with health professionals and support staff (*n* = 30), from the participating practices prior to, during (brief quarterly interviews) and at the end of the intervention period, to identify their experiences of the intervention including: any intervention barriers or enablers; how the intervention affected their ability to respond to women’s needs, monitor performance, anticipate needs and learnings; and ideas for intervention enhancement.Interviews with women with T2DM at the end of the observation period (*n* = 15), addressing their views on any reproductive information or support they have received and whether their understanding or views about pregnancy have changed.Interviews with up to 10 women who become pregnant during the observation period including women from practices that were and were not exposed to the intervention.We will ask practices who decline participation their reasons for this, and we will aim to conduct a short interview with staff from these practices (*n* = 5–10, depending on number of decliners).

The interviews will be conducted, either face-to-face or telephone (based on preference), and digitally recorded. Digital records will be transcribed verbatim in preparation for analysis using Framework Analysis [36]. This analysis will also identify emergent themes which can be integrated with the underpinning theoretical models (CAS, NPT and COM-B). A questionnaire will be sent to every practice in the participating boroughs to establish any changes to the practices that might impact on care delivery, to identify any contaminating or extraneous factors.

Quantitative data for the process evaluation will include:A report of the number and characteristics of eligible practices that accept or decline participation.A brief electronic questionnaire to all relevant health professionals (identified at practice sign-up) in participating practices to measure their baseline knowledge and beliefs in relation to reproductive health care in diabetes.A quarterly audit of intervention adherence based on recorded intervention utilisation as extracted from the intervention templates on the electronic records system.Exit questionnaires to all the health professionals and practice managers in the intervention practices, considering: NPT components [37, 38] following programme exposure; intervention satisfaction and utility; three strengths, weaknesses and areas for improving the programme; and a follow-up measure of health professional knowledge and beliefs in relation to reproductive care to assess learning.

The audit and questionnaire data will be analysed to provide insights on the acceptability, utilisation, reach and satisfaction of the programme. Intervention fidelity will be assessed from the audit data detailing the delivery of the different intervention components.

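### Reproductive reviews are identified by activation of the intervention's own template, so their change from the 12-month pre-exposure baseline mixes new recording with changed care

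*Protocol article*

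**What the plan says.** **The instrument.** Under Data collection, the protocol article states that the audit data of Table 1 will be "extracted from participating practices using an electronic template that we will install in the participating practices electronic record keeping system". Among the items identified this way it lists "reproductive assessments (activated on template") and "PPC care-plan initiation".

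**The intervention.** The quantitative part of the process evaluation, later in the same section, measures adherence from "recorded intervention utilisation as extracted from the intervention templates on the electronic records system". Under Development of PREPARED, the article says "PREPARED involves installing interventions to promote PPC within the electronic management systems of general practices in primary care". It names among the components "decision support systems to prompt pregnancy review in primary care" and "reproductive intention and pregnancy reviews with collaborative care-planning for all eligible women".

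**The baseline.** Data collection also says: "The hospital and practice level data will be extracted at baseline (12-month pre-PREPARED exposure"), followed by monthly extraction for run charts. Study design likewise takes performance in the 12 months before the intervention as the baseline for the repeated performance measures.

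**The use.** Review with care plan is the first process line of Table 1 and is marked for both systemic and practice-level performance. Data collection defines the unit of observation as a care event that has been recorded, and says the pooled analysis will show the intervention's effect on whether care processes are activated.

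**The concern.** A reproductive review is counted when the template is activated, and the template arrives with the intervention. A discussion of pregnancy intention held before installation leaves no template activation, so under the stated definition it is not counted. After go-live the same discussion is counted, and it is also prompted and fed back to the practice. Recording and exposure therefore start together.

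At stake is the before–after reading of reviews, and probably of care plans and contraception advice. The first study objective covers effects on care processes as well as outcomes, and Data integration and analysis promises a robust estimate of intervention effects. For these measures the contrast would be biased towards the programme.

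**Working it through.** **1. The template and the intervention.** Data collection describes a template that the study installs. The process evaluation speaks of intervention templates on the record system and reads adherence from them. Prompts in the record system, and reviews with care planning, are named components. Together these make the measuring instrument part of the intervention.

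**2. Definition against baseline window.** Reviews are those activated on the template. The baseline window lies wholly before exposure. Template activations in that window number zero, whatever care was given. The article describes no other way of finding earlier reviews.

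**3. Which items are touched.**
- Reproductive reviews: directly, because the definition says so.
- Care plans and contraception advice: by inference only. They are Table 1 items from the same extraction, and care plans share a Table 1 line with reviews, but neither is labelled as template-activated.
- The PREPARED care pathway and resources: a zero baseline is true, because they had not yet been offered.
- HbA1c, 5 mg folic acid and potentially teratogenic prescriptions: not defined by activation. Hospital booking data also cover them in women who become pregnant.

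**4. Is there a concurrent check?** The comparisons with unexposed practices (Data collection; Data integration and analysis) cover antenatal, pregnancy and birth data. None is described for reviews or care plans. The questionnaire to all practices asks about changes that might affect care delivery and is not described as counting earlier reviews.

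**5. Illustrative size.** The one relevant figure in the plan reproduces: 30 practices × 25 women = 750 (Study setting, sample size and participants). The documents give no review rate and no capture probability, so the rest is assumption. Let r be the true review rate, the same in both periods, s0 the capture before installation and s1 the capture after.

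Spurious rise = r × s1 − r × s0 = r × (s1 − s0)

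With s1 = 0.9, in percentage points:

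| True rate r | s0 = 0 | s0 = 0.25 | s0 = 0.5 | s0 = 0.9 |
|---|---|---|---|---|
| 5% | 4.5 | 3.25 | 2 | 0 |
| 10% | 9 | 6.5 | 4 | 0 |
| 20% | 18 | 13 | 8 | 0 |
| 30% | 27 | 19.5 | 12 | 0 |

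For r = 20% and s0 = 0, the recorded count goes from 0 to 750 × 0.20 × 0.9 = 135 women with no change in care. With s1 = 0.8 and s0 between 0 and 0.10, the same r gives a rise of 14 to 16 points (from 0–2% to 16%).

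If care does improve, say from 10% to 30%, the recorded rise is 0.30 × 0.9 − 0.10 × s0. That is 27 points with s0 = 0, and 18 points with s0 = 0.9. On those assumptions, unequal capture adds 9 points to a real gain.

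**The case against.** The strongest reply is that this is detail a journal article leaves to the full protocol. The article says that all practice audit data, glycaemic control included, are extracted with the template. If that meant nothing earlier could be retrieved, baseline HbA1c would be empty too. A planned 12-month baseline therefore implies that the tool can search older records. Part of this stands: the extraction may well read earlier codes, and the baseline for reviews may exceed zero. It does not remove the point. The article states a definition for reviews and a baseline window that do not fit together. Free or sporadic coding before installation is also unlikely to capture reviews as completely as a prompted, structured template.

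Three stronger readings are tempting, and the documents do not support them.

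- **That the main evidence of impact is compromised.** The 30% target rests on HbA1c, 5 mg folic acid and teratogenic therapies. The health economics section takes its outcomes from the same three. None is defined by template activation, and the review and care-plan measures are additional monitoring.
- **That one continuous chart runs across go-live.** The text gives a baseline extraction followed by monthly extraction over the 18-month observation period. It describes no monthly series spanning go-live, and its explicit baseline-to-final analysis concerns the PPC criteria.
- **That optimisation decisions are biased in the same way.** Those decisions rest on reviews during follow-up and on differences between practices, and after go-live all practices use the same instrument.

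The plan also already uses template data to audit adherence and fidelity, so part of the remedy is in place.

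**Conclusion.** The point holds in a limited form. For reproductive reviews, the stated definition combined with the stated baseline gives a contrast that mixes recording with care and favours the programme. For care plans and contraception advice the same is probable but inferred. It does not extend to the 30% target, to pathway activation or PREPARED resources, or to comparisons made wholly after go-live.

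The size cannot be determined from the documents. The illustrative 2 to 27 points assume a constant true rate of 5–30%, 90% capture after installation and 0–50% before; with equal capture the artefact is nil. The direction assumes only that capture rises once the template is in use. The change is worth making because it is cheap and affects the first measure in Table 1.

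**What to change.** Limit baseline-to-follow-up process comparisons to items that can be recorded independently of the template in both periods: 5 mg folic acid prescriptions, HbA1c tests and results, potentially teratogenic prescriptions and contraception prescriptions. The article does not say how these are held in practice records, so the team should confirm that they are available for the baseline year.

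Alternatively, define reviews and care plans by record codes available in both periods, list those codes, and apply them identically before and after installation. This helps only if capture by those codes is reasonably alike in the two periods.

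Report template-defined items from go-live as uptake or fidelity, not as change from baseline. The first quarter after go-live should not stand in as a baseline, because those practices are already exposed.

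The cost is a change of analysis wording and, for the second option, a code list. No additional patients are needed. The downside is that no baseline claim can be made for template-only items.
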